	**Acupoints location**
Daling (PC7)	Located at the midpoint of the transverse stripes of the palm of the hand, between the palmar longus tendon and the flexor carpi radialis tendon.
Hegu (LI4)	Located between the first and second metacarpal bones on the back of the hand, at the midpoint of the radial side of the second metacarpal bone.
Functional point 1	Location roughly equivalent to the position of the elbow-liu (LI12) point in the Large Intestine meridian of the hand
Functional point 2	Location roughly equivalent to the location of the Waiguan (SJ5) in the triple energizer meridian of the hand.

#### Control Group

Acupoints used were Jianyu (LI15), Quchi (LI11), Shousanli (LI10), Waiguan (SJ5), Hegu (LI4), and Baxie (EX-UE9). Operation: Sterile acupuncture needles of (single tube needles) 0.30 mm × 40 mm milli-needles (produced by Wuxi Jiajian Medical Instruments Co., Ltd.) were used. The conventional straight puncture method was used. Routine disinfection of acupuncture site, direct puncture with a 0.30 × 40 mm filiform needle, 15~25 mm depth of penetration, and LI10 and LI4 were connected to the G6805-a electroacupuncture instrument, sparse and dense waves, the intensity is as tolerated by the patient, and then the needle is retained for 30 minutes. The treatment was performed once a day, 5 times a week for 4 weeks. The curative effects were evaluated before and after treatment.

### Outcome Assessments

All the data collectors received strict professional training to assess the degree of clinical neurological deficits and upper extremity motor function of the patients before treatment, after one course of treatment and after three courses of treatment and to fill in the modified Ashworth score (MAS), clinical neurological deficit score (CSS), Fugl-Meyer upper extremity function assessment (FMA-UE), and the Modified Barthel Index (MBI) score to established case experimental forms of patients.

#### Primary Outcomes

The main result is the MAS, which is the most widely used clinical spasm scale (32). It is usually used to obtain the baseline evaluation of increased muscle tone, monitor the course of the disease, determine the effectiveness of drugs, and rehabilitation interventions, so as to reduce the overall increase of muscle tension, normalize the muscle tone of the selected muscle group, and guide physical therapy and other treatment decisions. It has the advantages of simplicity, time saving, and convenient operation. It is divided into 6 levels, i.e., 0, I, I +, II, III, and IV. Scoring methods, i.e., 0, 1, 2, 3, 4, and 5 points, represent 0, I, I +, II, III, and IV, respectively. The higher the MAS score, the more serious the spasticity. Compared with the lower limbs, the reliability of the upper limbs is better (33). The specific contents of MAS are shown in Table 3.

**Table 3 T3:** The modified Ashworth score (MAS)-specific scoring rules.

	**Modified Ashworth Scale**
0	No increase in muscle tone
1	Slight increase in muscle tone, manifested by a catch or by minimal resistance at the end of the range of motion (ROM) when the affected part(s) is (are) moved in flexion or extension
1+	Slight increase in muscle tone, manifested by a catch, followed by minimal resistance throughout the remainder (less than half) of the ROM
2	More marked increase in muscle tone through most of the ROM, but affected part(s) easily moved
3	Considerable increase in muscle tone, passive movement difficult
4	Affected part(s) rigid in flexion or extension

#### Secondary Outcomes

The FMA-UE, CSS, and MBI were secondary outcome indicators.

The FMA-UE is often a widely used evaluation tool for evaluating upper extremity motor function during stroke rehabilitation. It can effectively, stably, and sensitively reflect the changes in patients' dysfunction with good reliability and validity (34, 35). Evaluate the flexion, coordination, range of motion, stability, and coordination of each joint of the patient's upper limb, which is composed of 33 items in four parts: hand, wrist, elbow, and shoulder, with a total score of 66. The lower the score, the more serious the upper extremity dysfunction. The minimum clinically important difference (MCID) of FMA-UE was 4.25–7.25 points (36). That is, if the difference in upper extremity motor function score before and after treatment is >MCID, it is considered that the upper extremity motor function of the patient has been improved, the treatment is effective and can surpass the random error (37).

The CSS was determined by the “Fourth National Conference on Cerebrovascular Diseases” (1995), which is mainly to evaluate the curative effect and is divided into basic cure (the score of functional defect was decreased by 91–100%, and the degree of disability was grade 0), significant effect (the score of functional defect was decreased by 46–90%, and the degree of disability was grade 1), improvement (the functional defect score was decreased by 18–45%), and ineffective (the functional defect score decreased by about 17%). The score is simple and easy to use (38).

The MBI is a standard scale that is widely used to evaluate the dysfunction of basic activities of daily living, which consists of 10 daily life activities, such as bathing, toilet, eating, and dressing, with a total score of 100. The higher the score, the better the self-care ability in daily life (39).

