Our group through reviewing the literature and combining with a summary of clinical practice experience found that the use of functional acupuncture (FA) can effectively improve forearm spasticity and hand dysfunction after stroke (24–26), but the efficacy of ULS needs to be further verified. FA is a new acupuncture method that combines traditional acupuncture (TA) with modern rehabilitation theory and selects two common acupoints and two functional points to maximize the recovery of patients' various functions (27). FA can enhance sensory transmission, simplify acupoints, and have a great effect. It can be divided into three steps: rapid needling of the acupoint Daling (PC7), penetrating needling of the acupoint Hegu (LI4), and electrical stimulation of the functional acupoint. After rapid needling at PC7, the contracture fingers can be relaxed to a state of no flexion, passive activity, and no resistance and can last for several hours (28). The penetrating needling of LI4 to Houxi (SI3) can directly alleviate the spasticity of finger flexor muscle and indirectly excite and stretch the extensor tendon of a finger. By repeatedly stimulating the flexor tendon, the spasticity can be alleviated and the effect of improving finger dysfunction can be achieved (18, 29). In this state, the use of functional acupoint electrical stimulation can quickly improve the overall function of the upper limb. Then this topic is mainly to study the clinical efficacy of FA in the treatment of ULS after ischemic stroke.

In recent years, clinical experiments and basic research have found that acupuncture has an obvious therapeutic effect on ULPSS, it is considered by the World Health Organization (WHO) as an alternative and complementary strategy for the treatment and improvement of stroke (23), but the efficacy differences between different acupuncture methods are uncertain. Few trials involve the comparison of different acupuncture methods to verify the efficacy differences between different acupuncture interventions. In this study, FA was used to treat ULS after ischemic stroke, verifying the efficacy and rehabilitation significance of FA, which makes up for the study on the lack of different acupuncture methods in this disease, enriching the treatment of the ULSPSS, and providing a reference for clinical treatment of this disease.

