### Sample Size

The purpose of this study was to evaluate the efficacy of FA in the treatment of ULPSS. According to previous research and clinical experience, the effective rate of TA is about 65%, and the effective rate of FA will probably reach 85% (31). The significance test level is 0.05, and the test power is 0.9. The sample size is calculated by using:

$$\begin{array}{l} N=P\left(1-P\right){\left(\frac{\alpha +\beta }{\delta }\right)}^{2} \end{array}$$

where N is the required sample size for each treatment group, and the sample size of each group is equal. When α is 0.05 and β is 0.1, the normal distribution quantile table shows that:

$$\begin{array}{l} Z_{\text{α}/2}=1:645 \end{array}$$

and

$$\begin{array}{l} Z_{\text{β}/2}=1:282 \end{array}$$

P_0_ and P_1_ represent the original curative effect and the expected curative effect, 65 and 85%, respectively. δ represents the mean difference between two groups, by substituting the above parameters and values into the formulas, 49 cases will be needed for each group. Accounting for a 10% expulsion rate, the final estimated sample size will be about 54 cases per group (108 in total).

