### Interventions

The experiment was divided into two groups: the experimental group and the control group. The two groups of patients received different treatments five times a week for 4 weeks. At the same time, each patient received symptomatic treatment and supportive treatment. On the basis of routine rehabilitation treatment, acupuncture was used in the groups. The experimental group was treated with FA, and the control group was treated with TA.

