### Statistical Analysis

After all the experimental data are verified to be correct, SPSS19.0 statistical software is used for statistical analysis. Classified variables will be analyzed using Pearson's χ^2^ test or Fisher's exact test, and continuous variables will be evaluated using Student's *t*-test or an appropriate non-parametric method. The statistical results are measured by the mean ± standard deviation (SD; *x* ± s); when comparing within or between groups, tests for normality and homogeneity of variance are performed prior to data analysis for each group. If the data satisfy normal distribution and homogeneity of variance, the *t*-test will be used for comparisons between two groups, and the least significant different (LSD) or Student-Newman-Keuls (SNK) method will be used for multiple comparisons. Instead, the rank-sum test will be used for non-normality or non-uniformity of variance. Set the test level as 0.05, *p* < 0.05, and the difference was statistically significant.

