
### The Combination of Subjective and Objective Outcome Measures

In addition to the scale evaluation selected in this study, we also adopted the evaluation methods, such as surface electromyography (sEMG) and electrophysiological measurement (H-reflex), and adopted a combination of subjective and objective methods to reduce the impact of a series of human interventions on the experimental results and make the study more convincing (44).

One important limitation of our study is an acupuncture trial, it is impossible to perform a double-blind procedure. In order to reduce this bias, each group of patients will receive treatment at different times in different rooms, and communication between each group of patients is prohibited. In addition, all acupuncturists participating in this study will receive unified training, strictly standardize acupuncture operation, and eliminate the error of the study to the greatest extent.

In conclusion, this report describes a randomized controlled trial that systematically evaluates the rehabilitation effect of FA on patients with ULPSS. To observe the clinical effect of functional acupuncture on ULPSS, and to determine whether FA can effectively improve the ULS and improve the extremity motor function and self-care ability of patients after stroke. This study not only provides a new idea for the clinical treatment of ULPSS but also provides effective experimental support and a theoretical basis for the clinic.

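### The before-after FMA-UE rule, the unranked within-group comparisons and an objective without a comparator permit an absolute efficacy claim for FA that an FA-versus-TA design cannot support

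*Protocol article*

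**What the plan says.** **Comparison.** Trial Design and Setting says the efficacy of the experimental group is analysed against the control group. Sample Size is built on effective rates of 85% for FA and 65% for TA. Statistical Analysis names a t-test between the two groups, with a rank-sum test as fallback. The Introduction motivates the trial by noting that "the efficacy differences between different acupuncture methods are uncertain".

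**Arms.** Interventions states: "On the basis of routine rehabilitation treatment, acupuncture was used in the groups". It continues: "The experimental group was treated with FA, and the control group was treated with TA". Both arms also receive symptomatic and supportive treatment. No arm goes without acupuncture.

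**Before-after rule.** Secondary Outcomes reports: "The minimum clinically important difference (MCID) of FMA-UE was 4.25–7.25 points". If a patient's change exceeds the MCID, motor function is considered improved and "the treatment is effective and can surpass the random error".

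**Within-group comparisons.** Statistical Analysis says that "when comparing within or between groups, tests for normality and homogeneity of variance are performed", and sets one test level of 0.05 for the whole paragraph. It does not say which type of comparison answers the objective.

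**Objective.** Sample Size states: "The purpose of this study was to evaluate the efficacy of FA in the treatment of ULPSS". The opening of the Discussion has a similar sentence on efficacy and safety. The closing paragraph of the Discussion gives the aim as "to determine whether FA can effectively improve the ULS and improve the extremity motor function and self-care ability of patients after stroke". None of these three sentences names TA.

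**The concern.** An MCID grades how large a change is. It does not say what caused it. The Secondary Outcomes sentence moves from a statement about the patient (function has improved) to a statement about the treatment (it works), and the design does not license that step. A four-week change in the FA arm contains spontaneous recovery, routine rehabilitation, symptomatic treatment, any regression to the mean, and acupuncture. Without an arm that differs only by having no acupuncture, these cannot be separated.

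The loose sentence matters more because the objective is also worded without a comparator and within-group comparisons are foreseen without being ranked below the between-group test. If FA and TA turn out alike, a report could still answer the question in the closing paragraph of the Discussion with a yes, citing significant change within the FA arm or the share of patients above the MCID, and could say that it followed the protocol. What is at stake is the conclusion the trial is allowed to draw, not the data it collects.

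**Working it through.** **1. What the design identifies.** Write the mean change in each arm as

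- FA arm: B + E(FA)
- TA arm: B + E(TA)

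where B is the change from recovery, rehabilitation and supportive care common to both arms, and E is the effect of each acupuncture method. Randomisation makes B equal in expectation, so the between-arm difference is E(FA) - E(TA). The within-FA change is B + E(FA). With no acupuncture-free arm, E(FA) cannot be isolated, either from within-arm change or from the between-arm difference.

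**2. Inputs.** From the documents: 54 per arm, test level 0.05, TA effective rate 65%, MCID range 4.25 to 7.25. The documents give no background change, no SD of change and no time-since-stroke window, so every value of background change below is an assumption, shown as a range. No paired test is named either; a paired t-test is assumed as the usual form of a within-group comparison. The plan has no figure of its own for before-after change to reproduce.

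**3. Within-arm test.** Assume the same mean change of d SDs of change in both arms, with FA and TA identical. A two-sided paired t-test with n = 54 has 53 degrees of freedom, critical value 2.006 and noncentrality d × √54.

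| d (assumed) | d × √54 | P(significant improvement within FA arm) |
|---|---|---|
| 0.3 | 2.20 | 0.58 |
| 0.5 | 3.67 | 0.95 |
| 0.8 | 5.88 | over 0.99 |

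With 49 per arm, the number before the allowance for losses, the figures are 0.54, 0.93 and over 0.99.

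**4. Between-arm test on the same data.** The common change cancels. In simulation with FA identical to TA and 49 per arm, the two-sample t-test rejected in 4.5% to 5.1% of trials and favoured FA in 2.3% to 2.7%, whatever the value of d. At 54 per arm the result is the same, about 2.5% in favour of FA.

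**5. The MCID label.** Assume FMA-UE gains that are normal with mean m and SD s. The share of patients above cut-off c is 1 - Φ((c - m)/s).

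- m = 5, s = 5: above 4.25, 1 - Φ(-0.15) = 56%; above 7.25, 1 - Φ(0.45) = 33%.
- m from 3 to 7 and s of 5 or 7: 40% to 71% above 4.25, and 20% to 49% above 7.25.

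If this gain were all background, the sentence in Secondary Outcomes would still say of each such patient that treatment was effective.

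**6. With the protocol's own rate.** If FA were no better than TA at 65%, about 0.65 × 54 = 35 of 54 FA patients would be classed as effective. The Sample Size section does not tie this rate to the FMA-UE, so this is an illustration only. A chi-squared comparison of two arms at 65% (49 per arm) would favour FA in about 2.4% of trials.

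**The case against.** The strongest reply is that the trial is already set up as a comparison. The efficacy analysis against the control group, the 85% versus 65% sample size, the named two-group test and the stated rationale are all comparative. TA was deliberately chosen as the comparator, which is a legitimate active-control design. The MCID sentence describes one secondary outcome, labels individual patients, and is not turned into an arm-level decision rule; the primary outcome, the MAS, carries no such rule. The within-group phrase occurs in a sentence about checking assumptions, names no paired test and ties no conclusion to one. Details of responder analysis are often left to a statistical analysis plan.

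Most of this stands, and it rules out a stronger reading. A reader might infer that the plan judges FA by before-after change and would answer its question with a yes even if FA added nothing. The documents do not support that. When FA equals TA, the planned between-group comparison favours FA only about 2.5% of the time. If FA added nothing to rehabilitation while TA worked, that comparison would tend to favour TA.

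What the reply does not remove is the stated text. The causal sentence and the purpose statements without a comparator are in the article; they are not details deferred elsewhere. The between-group test does not cure them either. A positive FA-TA difference would still not show that FA works in absolute terms, and a null difference would leave the before-after sentence available as an answer.

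**Conclusion.** The point holds as one about what may be concluded, not about the randomised comparison, which is sound in kind. Three statements together (the MCID sentence, the unranked within-group comparisons and the objective without a comparator) permit an absolute efficacy claim for FA that the design cannot support, including when FA and TA do not differ.

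The size depends on a background change that the documents do not give. The contrast between about 58% to over 99% (within one arm) and about 2.5% (between arms, in favour of FA) rests on an assumed common change of 0.3 to 0.8 SD and an assumed paired t-test. These are not error rates of the planned FA-TA comparison. They show how far the two readings that the text allows can diverge on the same data. The correction should be made because it is cheap and changes the permitted conclusion.

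**What to change.** - **Objective and conclusion** (Sample Size, opening of the Discussion, closing paragraph of the Discussion): word them as FA plus routine rehabilitation compared with TA plus routine rehabilitation, with efficacy judged only on the between-group difference.
- **Secondary Outcomes, FMA-UE:** replace the statement that the treatment is effective with one that the patient is counted as improved, and compare the proportion improved between arms. That comparison needs a single cut-off fixed in advance, since the text gives a range.
- **Statistical Analysis:** report within-group changes descriptively, with no p-value used as evidence of efficacy.
- **Interpretation:** state that a null FA-TA difference does not show that either method works.

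This needs no new data, patients or arms. The cost is a narrower claim: the trial can say how FA compares with TA, but not whether FA works in absolute terms.

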**Method:**

This is a parallel design and randomized controlled trial. We selected 108 patients who met the predefined criteria and randomized them into two groups, the experimental group and the control group. The experimental group receives FA and routine rehabilitation treatment. The control group received traditional acupuncture (TA) and routine rehabilitation treatment. All patients received 20 courses of treatment for 4 weeks, and the modified Ashworth score (MAS), clinical neurological deficit score (CSS), Fugl-Meyer upper extremity function assessment (FMA-UE), and the Modified Barthel Index (MBI) scores were evaluated before and after treatment.

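### The CSS secondary endpoint has no fixed form: it is recorded as a score but described as four ordered classes, and the choice decides the test, with order-blind chi-square or Fisher for the classes

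*Protocol article*

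**What the plan says.** All references are to the protocol article.

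- **Abstract, Method.** The CSS is listed with the other scales as a measured score: "clinical neurological deficit score (CSS), Fugl-Meyer upper extremity function assessment (FMA-UE), and the Modified Barthel Index (MBI) scores were evaluated before and after treatment".
- **Outcome Assessments.** Data collectors enter the CSS on the case forms together with the other scales: "clinical neurological deficit score (CSS), Fugl-Meyer upper extremity function assessment (FMA-UE), and the Modified Barthel Index (MBI) score". Table 1 schedules it at allocation and at week 4.
- **Secondary Outcomes.** The CSS is described by its use as a response rating, "which is mainly to evaluate the curative effect and is divided into basic cure", significant effect, improvement and ineffective. These are defined by the percentage fall in the deficit score, with a disability grade attached to the top two. The same paragraph ends by still calling it a score: "The score is simple and easy to use".
- **Statistical Analysis.** The test follows the type of variable: "Classified variables will be analyzed using Pearson's χ^2^ test or Fisher's exact test". Continuous variables go to Student's t-test or a non-parametric method. The rank-sum test is named as the fallback when normality or equal variance fails. Ordered classes are not mentioned, and neither is the CSS.

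**The concern.** The classes are built from the score, so both forms can be produced from the same case form. What is not settled is which of them is the endpoint. Because the analysis rule is keyed to variable type, that gap is also a gap in the test: a score leads to a t-test or rank-sum test, and four classes lead to chi-square or Fisher.

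The class route has a second weakness. The four classes have a clear order, and the question is whether one arm sits higher on it. A Pearson chi-square on a 2×4 table spends 3 degrees of freedom on any kind of difference and treats the classes as unordered labels.

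Two things are at stake for this endpoint: loss of power if the literal class rule is followed, and a choice between two supportable analyses that could be made after the data are seen. Both would remain if the class boundaries were worded perfectly.

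**Working it through.** **Inputs from the article.** Arm sizes come from Sample Size. The printed formula with P = 0.65 gives 0.65 × 0.35 × ((1.645 + 1.282)/0.20)² = 48.7, so 49 per arm, and 49 × 1.10 = 53.9, so 54. The 49 and 54 are used here only as arm sizes. The 65% and 85% effective rates in that section are not tied to the CSS; they are borrowed as an illustrative contrast. The test level is 0.05, taken as two-sided.

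**Inputs assumed.** The article gives no CSS class distribution, no SD of the percentage fall and no baseline mean or SD. The ranges used are stated below. Classes were cut at falls of 17.5, 45.5 and 90.5%, because the printed bands leave gaps. The disability-grade conditions were left out.

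**1. Same four classes, unordered against ordered test.** Proportional odds, with OR = (0.85/0.15)/(0.65/0.35) = 3.05. Control classes, from ineffective to basic cure, were 35/35/25/5, 35/30/25/10 and 35/25/25/15%.

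| Effect | Per arm | Chi-square (3 df) | Rank-sum |
|---|---|---|---|
| OR 3.05 | 49 | 0.70–0.72 | 0.84–0.86 |
| OR 3.05 | 54 | 0.75–0.77 | 0.89 |
| OR 2.0 | 49 | 0.30–0.33 | 0.46–0.48 |

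The loss is 12 to 15 points at OR 3.05 and 14 to 16 at OR 2.0. A separate run at OR 2.5 with 49 per arm gave 0.51 against 0.69, or 18 points, so 16 is not a ceiling.

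*Analytic check.* With noncentrality (1.96 + z)², where z is the normal quantile of the 1-df power, the same signal was tested on 3 df. Power 0.80 falls to 0.645 and 0.90 falls to 0.784. Over 1-df powers of 0.5 to 0.9 the loss is 12 to 17 points.

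**2. Four classes against the score.** The percentage fall is normal with SD 20 to 30 points. Arm means are 17.5 + SD × 0.385 and 17.5 + SD × 1.036, so that 65% and 85% exceed the lowest cut. At SD 25 these are 27.1 and 43.4. The baseline CSS has mean 20 and SD 4 to 8. Results for 49 per arm at the full shift:

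| Analysis | Power |
|---|---|
| Four-class chi-square | 0.66–0.72 |
| Post-treatment score adjusted for baseline | 0.84–0.89 |
| Change from baseline, t-test | 0.74–0.84 |
| Post-treatment score, unadjusted t-test | 0.45–0.80 |

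At three quarters of that shift, the adjusted score has about 0.61 to 0.65 against 0.40 to 0.47 for chi-square. Over both shifts and both arm sizes, the classes lose roughly 13 to 24 points to the adjusted score; the larger losses come at the smaller shift. The last row runs the other way in places: with a baseline SD of 8 and an SD of the fall of 20, the unadjusted score has 0.45 against 0.70 for chi-square.

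**3. Do the analyses disagree?** With 49 per arm, the four-class chi-square and the adjusted score fall on opposite sides of 0.05 in about 19 to 29% of simulated trials. With no true difference, at least one of the two is significant in about 7 to 9% of trials.

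*Worked example on the classes alone, 54 per arm.* Take 19/19/13/3 against 10/18/19/7, from ineffective to basic cure.

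- Chi-square: expected counts are 14.5, 18.5, 16 and 5 in each arm. The statistic is 2 × (1.397 + 0.014 + 0.563 + 0.800) = 5.55 on 3 df, p = 0.136.
- Rank-sum: mid-ranks are 15, 48, 82.5 and 103.5. The control rank sum is 19×15 + 19×48 + 13×82.5 + 3×103.5 = 2580 against an expected 2943. The tie-corrected variance is 24,201, so z = −2.33 and p = 0.020.

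**The case against.** The best case against has four parts.

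- **There is no contradiction.** A score must be recorded before and after treatment before any class can be assigned, and Secondary Outcomes itself still calls the CSS a score. A reader might infer that the sections clash outright. They do not: the classes derive from the score, and what is missing is the statement of which form is compared. This part stands.
- **Detail may sit elsewhere.** Which summary of a secondary scale is tested is often left to the full protocol or the SAP. Statistical Analysis never names the CSS, so sending the four classes to chi-square is a literal reading and not a declared plan. That limits the point. It does not remove it, because the article does state a rule by variable type, and that rule gives ordered classes an order-blind test.
- **The power figures are not the trial's own.** A reader might take the loss as a known quantity. The article supports no single figure, and against an unadjusted post-treatment score the sign can change. This stands too, so only ranges under stated assumptions are given.
- **Chi-square is valid.** It holds its error rate, and the class proportions still show which arm did better. A reader might infer that the choice of form could reverse the conclusion. In the worked example the direction is the same under both tests; what moves is the p-value, across 0.05.

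A reader might also extend the point to the FMA-UE, where an MCID is quoted. The article uses it to interpret a patient's change and states no comparison of responder proportions, so there is nothing to correct there.

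**Conclusion.** The point holds as an unfixed endpoint form combined with a test rule that does not suit one of the two forms. For effects at or somewhat below the 65% versus 85% contrast, with 49 to 54 per arm, the four-class chi-square gives up roughly 12 to 16 points of power against a rank-sum test on the same classes, and roughly 13 to 24 points against the baseline-adjusted score. Choosing between chi-square and the adjusted score after seeing the data would lift the false-positive rate from 5% to about 7 to 9%.

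These sizes rest on assumed class splits, SDs and baseline spread, on borrowed effective rates, and on classes simulated without the disability grades. The mismatch between ordered classes and an unordered test needs none of those assumptions. The CSS is one of three secondary outcomes, and the primary MAS comparison is untouched. The change is worth making because it is cheap, not because the trial depends on it.

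**What to change.** - **Secondary Outcomes.** State that the CSS endpoint is the end-of-treatment CSS score, compared between arms with adjustment for the baseline CSS score, and that the four response classes are presented descriptively. Tie the score to the week 4 assessment in Table 1, since Outcome Assessments words the assessment times differently. The baseline adjustment matters, because the unadjusted score can do worse than the classes.
- **Statistical Analysis.** If the classes are to be tested as well, state that ordered classes are compared by a rank-sum test or a proportional-odds model instead of chi-square or Fisher, and label that result supportive.

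The cost is about one sentence in each section. Table 1 already schedules both CSS assessments, so no data, visits or patients are added. The downside is that the familiar four-class curative-effect table is no longer the tested result. The choice should be fixed before outcome data are examined.
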